### Sample size

The study was designed to detect an increase from 85% to 95% in the proportion of culture-confirmed pulmonary TB cases initiated on appropriate treatment within 30 days. Sample size was calculated with the equation of Hayes and Bennett, using the coefficient of variation (κ) [26]. With κ = 0.05 and a cluster size of 12 culture-positive cases, we would need 16 clusters and 188 culture-positive TB cases in each arm to detect this difference with 95% confidence and 80% power. We assumed 10% of individual participants would be lost to follow-up at 60 days, so we would need 208 culture-positive TB cases in each arm. Based on the assumption that 25% of TB suspects would have a positive MGIT culture, we would require enrolment of 1,664 TB suspects. The total sample size will therefore be 32 clusters and 1,664 individual participants.

The coefficient of variation (κ) is small, but as the clusters are clinic time blocks rather than geographic areas or health care facilities, minimal variation is expected between clusters. This value of κ corresponds to a range of proportions appropriately treated within 30 days in the district hospital laboratory arm of 77-94%.

For the secondary endpoint of all-cause mortality within 60 days, the analysis will incorporate all participants (all suspects), regardless of presence or absence of TB disease. The sample size of 32 clusters and 60 participants per cluster gives approximately 80% power to detect a 33% reduction in mortality from 12% in the district hospital laboratory arm to 8% in the point-of-care arm, with 95% confidence.

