### Statistical analysis

Analysis of baseline characteristics will be performed to characterise the study population and to identify baseline imbalances between the study arms in order to decide whether any covariates need to be adjusted for in the final analyses. The baseline data will include: age, sex, body mass index (BMI), history of previous TB, HIV infection status, CD4+ cell count, and use of antiretroviral therapy and isoniazid preventive therapy.

All final analyses will be intention-to-treat analyses performed at the individual level taking account of within-cluster correlation. The definition of TB cases for the primary outcome will be based on MGIT culture positivity. The proportion of TB cases initiated on appropriate TB treatment within 30 days will be based on whether the appropriate treatment regimen was commenced within 30 days of the initial clinic visit—appropriate regimens are defined according to drug susceptibility pattern and with reference to national guidelines (Table 1) [27]. The primary analysis will include only TB cases not on TB treatment at the time of enrolment, i.e. excluding smear non-converters or failures still on treatment. The primary outcome is a binary variable (initiation of appropriate treatment or not) so univariate logistic regression will be performed as the primary analysis using generalised estimating equations (GEE) with a binomial distribution function and a logit link [28]. The odds ratio will be reported with 95% confidence intervals and a *p*-value from the Wald test. This method will allow for the correlation between observations (within clusters) without needing to specify a distributional assumption for the correlations. In addition, important individual-level characteristics that are unbalanced between arms will be included in the model as covariates. For the secondary outcomes with binary variables, GEE models will also be fitted with a binomial distribution function and a logit link. For the secondary outcomes with time-to-event measures, Cox proportional hazard models will be fitted with the shared frailty option to account for the cluster randomisation [29]. Hazard ratios will be presented with 95% confidence intervals.

**Table 1 T1:** Definitions of appropriate initial anti-TB drug regimen for primary outcome measurement

**Case definition***	**Appropriate initial anti-TB drug regimen**

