### Economic evaluation

In addition to evaluating the effectiveness of point-of-care positioning of Xpert MTB/RIF, data from the trial will be combined with those from a costing analysis to explore the cost-effectiveness of point-of-care placement. Health system costs will be obtained through monitoring of study expenditure and interviews with health service management. Collection of data relating to patient and household costs will be nested within the trial—this will involve additional data collected from a subset of patients at baseline and at the 2-month follow-up to determine direct and indirect costs incurred during the diagnostic process. The framework for costing analysis is presented in Table 2. The health system costs and patient costs will be combined with the outcome data to generate an average incremental cost per TB case appropriately treated.

**Table 2 T2:** Components of cost analysis

**Health service costs**	**Patient and household costs**
**Direct costs associated with diagnostic services**	**Direct costs**
***Fixed***	***Transport***
Building space	Transport to/from clinic (patient ± carer)
Utilities	Transport to/from hospital (patient ± carer)
GeneXpert machine	***Non-transport***
Staff training	Medication
Internal/external QC	OPD attendance
GeneXpert calibration	X-rays
***Variable***	GP consultation
Xpert MTB/RIF tests	Traditional healer consultation
Consumables (gloves, N95 masks)	
Specimen transport	
Staff work time (based on time analysis)	
GeneXpert maintenance	
**Direct costs associated with medical services**	**Indirect costs**
First-line TB therapy	Lost time (salary) at work (patient ± carer)
MDR-TB therapy	
Hospital admission	
OPD attendance	
Clinic attendance	

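### The primary GEE Wald test is named for 16 clusters per arm with no stated small-sample correction; run as named, its type I error is about 6.4-7% rather than 5%

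*Protocol article*

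**What the plan says.** The Statistical analysis section fixes the primary analysis as a univariate logistic GEE with binomial distribution and logit link. It continues: "The odds ratio will be reported with 95% confidence intervals and a *p*-value from the Wald test". The reason given for the method is: "This method will allow for the correlation between observations (within clusters) without needing to specify a distributional assumption for the correlations". The same GEE model is to be used for the binary secondary outcomes. The section names no variance estimator, reference distribution or degrees of freedom, and it does not say that a correction will be left out.

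The Sample size section uses the Hayes and Bennett formula with the coefficient of variation κ, for an increase from 85% to 95%: "With κ = 0.05 and a cluster size of 12 culture-positive cases, we would need 16 clusters and 188 culture-positive TB cases in each arm". The targets are a power of 80% and a confidence level of 95%. The total is 32 clusters. The section translates κ into a range of cluster proportions, 77-94%, for the district hospital laboratory arm only.

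**The concern.** The freedom from assumptions about the correlation comes from the empirical (sandwich) variance. That variance is estimated from between-cluster residuals. With 16 clusters per arm it is biased downwards and is itself noisy. Comparing the estimate with a normal quantile ignores the noise. Both errors act in the same direction: p-values too small and intervals too narrow.

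This is the only primary test, so the claimed 5% error rate rests on it. A related point is scale. The trial was sized for a difference in proportions, while the named test is on the log odds ratio, with one arm expected near 95%. The stated power therefore does not automatically carry over to the named test once its size is corrected.

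**Working it through.** **Inputs (Sample size section).** p0 = 0.85, p1 = 0.95, κ = 0.05, m = 12 cases per cluster, 16 clusters per arm, 95% confidence read as two-sided 5%, power 80%.

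**1. The plan's own figure.** Hayes-Bennett:

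c = 1 + (1.960 + 0.842)² × [p0(1−p0)/m + p1(1−p1)/m + κ²(p0² + p1²)] / (p1 − p0)²

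= 1 + 7.849 × [0.010625 + 0.003958 + 0.004063] / 0.01 = 1 + 7.849 × 1.8646 = 15.63, so 16 clusters.

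15.63 × 12 = 187.6, so 188 cases. Power of the formula at 16 clusters: Φ(√(15 × 0.01/0.018646) − 1.96) = 81.0%. The design reproduces.

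**2. Rough size of the error by hand.** With equal cluster sizes each cluster has leverage 1/16 in its arm, so the sandwich variance is too small by a factor of about 15/16. The critical value 1.96 then acts like 1.96 × √(15/16) = 1.898 on a t scale with 32 − 2 = 30 df. The two-sided tail area of t(30) at 1.898 is 6.7%.

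**3. Simulation.** 60,000 trials per scenario; beta-distributed cluster proportions with mean p and SD κp, κ = 0.05 in both arms; 16 clusters per arm; independence working correlation. Cluster sizes were fixed at 12, Poisson with mean 12, or Poisson with mean 11.75 (= 188/16). Kauermann-Carroll (KC) divides each squared cluster residual by (1 − leverage); Mancl-DeRouen (MD) divides by its square. Monte Carlo error is about 0.1 point for size and 0.2 point for power.

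| Test | Type I error, 85% / 90% / 95%, fixed 12 | Same, Poisson 12 | Power, fixed 12 | Power, Poisson 12 | Power, Poisson 11.75 |
|---|---|---|---|---|---|
| Log odds, ordinary sandwich, normal | 6.6 / 6.4 / 6.9% | 6.7 / 6.7 / 6.8% | 80.9% | 80.0% | 79.7% |
| Log odds, KC, t(30) | 4.8 / 4.6 / 5.0% | 4.8 / 4.9 / 4.9% | 76.3% | 75.2% | 74.6% |
| Log odds, MD, normal | 5.0 / 4.8 / 5.2% | 5.0 / 5.1 / 5.0% | 76.9% | 75.6% | 75.0% |
| Log odds, MD, t(30) | 4.1 / 4.0 / 4.1% | 4.1 / 4.2 / 4.1% | 74.0% | 72.4% | 71.9% |
| Risk difference, KC, t(30) | 5.1 / 4.9 / 4.8% | 5.1 / 5.1 / 4.7% | 81.8% | 81.0% | 80.3% |

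MD with t(30) over-corrects to about 4%, so its power is not the fair comparator.

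**4. Sensitivity.** Exchangeable GEE fits with the ordinary sandwich (1,500 trials per scenario, Monte Carlo error about 0.6 point) gave a type I error of 6.1-7.2%. A two-point distribution of cluster proportions gave 6.6% at 85% and 6.0% at 95%. With κ = 0.02 in the point-of-care arm, the power of the size-restoring log-odds tests (KC with t(30), MD with normal) is 84-86%.

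**5. Why the scale matters.** The expected effect in standard errors, using the design variances 0.012431 and 0.006215 per cluster, is:
- difference: 0.10 / √((0.012431 + 0.006215)/16) = 2.93
- log odds: ln(3.353) / √(0.012431/(16 × 0.1275²) + 0.006215/(16 × 0.0475²)) = 1.210/0.469 = 2.58

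These first-order values show only the direction; the normal approximation is crude near 95%, so power is taken from the simulation.

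**The case against.** The strongest reply is that a missing correction is read from silence. A Wald test with a corrected variance and a t reference is still a Wald test. The article condenses a fuller plan that is not shown, and such a plan commonly names the variance estimator and degrees of freedom. This stands to the extent that nobody can say the trial will use an uncorrected test. It does not remove the point: the article fixes the test and its justification, and in its ordinary form that test does not hold 5% with 32 clusters.

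Three stronger readings are tempting, and the document does not support them.

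- **That the stated 80% power is a mistake.** It is attributed to Hayes-Bennett and reproduces exactly. The article does not claim it for the log-odds test. The ordinary Wald test also reaches about 80%, though at inflated type I error.
- **That the corrected trial is clearly underpowered.** The shortfall of about 3-5 points needs κ = 0.05 in the point-of-care arm. The formula needs that value to give 188 cases, but the article interprets κ only for the laboratory arm. At 95%, two SDs either way would be 0.95 ± 0.095, or 85.5-104.5%, which passes 100%. With κ = 0.02 (91.2-98.8%) the corrected power is above 80%.
- **That the odds ratio is the wrong primary measure, or conflicts with the cost analysis.** The effect does look different by measure (odds ratio 3.35, risk ratio 0.95/0.85 = 1.12). But the logit odds ratio is a standard choice. The plan to "generate an average incremental cost per TB case appropriately treated" can use the arm proportions directly, and nothing says these will go unreported.

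**Conclusion.** The point holds as a limited one. The named primary test, with the ordinary sandwich variance and a normal reference, has a type I error of about 6.4-7%, an excess of roughly 1.5-2 percentage points. Its intervals are too narrow to match. This rests on 16 clusters per arm, about 12 cases per cluster, κ = 0.05 and beta-distributed cluster proportions; it falls to 6.0% in the mildest alternative tried. Time trends and the permuted blocks were not modelled.

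The sample size is correct by its own formula. The 80% belongs to a comparison of proportions. For the size-corrected log-odds test the figure is about 75-77% with κ = 0.05 in both arms and 84-86% with κ = 0.02 in the point-of-care arm. The binary secondary outcomes use the same model on the same 32 clusters, so the same mechanism applies; its size was not computed for them.

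**What to change.** State before analysis, for the primary GEE and the binary secondary GEE analyses: 'Standard errors use a small-sample corrected sandwich variance (Kauermann-Carroll). Tests and 95% confidence intervals use a t distribution with 30 degrees of freedom.' This keeps the odds ratio as the primary measure.

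In the Sample size section, say that the 80% power refers to a comparison of proportions by the Hayes-Bennett formula.

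Optionally, report a risk difference with the same correction beside the odds ratio. It has about 81-82% power at about 5% size with a mean of 12 cases per cluster (80% with 11.75), and it is on the scale used for the sample size. Replacing the primary effect measure is not required.

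The cost is wording and a software option. With equal cluster sizes, intervals on the log-odds scale widen by a factor of √(16/15) × 2.042/1.960 = 1.076, about 8%. No extra clusters or participants are needed to restore the type I error.

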**Methods/Design:**

This pragmatic cluster randomised clinical trial compared two positioning strategies for the Xpert MTB/RIF system: centralised laboratory versus primary health care clinic. The cluster (unit of randomisation) is a 2-week time block at the trial clinic. Adult pulmonary tuberculosis suspects with confirmed human immunodeficiency virus infection and/or at high risk of multidrug-resistant tuberculosis are enrolled from the primary health care clinic. The primary outcome measure is the proportion of culture-confirmed pulmonary tuberculosis cases initiated on appropriate treatment within 30 days of initial clinic visit. Univariate logistic regression will be performed as the primary analysis using generalised estimating equations with a binomial distribution function and a logit link.

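### The adjusted odds ratio is built from whichever covariates turn out unbalanced between arms, and the text does not say clearly whether it or the univariate result governs

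*Protocol article*

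**What the plan says.** All the relevant text is in the Statistical analysis section of the protocol article, and the Methods/Design paragraph of the abstract repeats the choice of primary model.

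- **Primary model.** "univariate logistic regression will be performed as the primary analysis using generalised estimating equations (GEE) with a binomial distribution function and a logit link". The abstract agrees: "Univariate logistic regression will be performed as the primary analysis using generalised estimating equations with a binomial distribution function and a logit link".
- **Reported result.** "The odds ratio will be reported with 95% confidence intervals and a *p*-value from the Wald test".
- **Purpose of the baseline comparison.** It is made partly "to identify baseline imbalances between the study arms in order to decide whether any covariates need to be adjusted for in the final analyses".
- **Candidate variables.** Eight are listed: "age, sex, body mass index (BMI), history of previous TB, HIV infection status, CD4+ cell count, and use of antiretroviral therapy and isoniazid preventive therapy".
- **Covariate rule.** After the primary model and its reporting are described: "In addition, important individual-level characteristics that are unbalanced between arms will be included in the model as covariates".

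**The concern.** A baseline difference between arms does not show that a variable predicts the outcome. A strong predictor that happens to be balanced is left out under this rule, and a weaker one that happens to differ may go in. The word *important* limits this, but a covariate must still look unbalanced to be used, so the adjusted model depends on the data observed.

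The scope of the rule is also unclear. The covariates are added to *the model*, when the only model described so far is the univariate primary one, and the earlier sentence applies the decision to the final analyses in general. If the univariate and adjusted odds ratios lead to different conclusions, the text gives no explicit order of precedence.

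Two features add to this. The Discussion says that blinding of patients and health care workers is not feasible. And an odds ratio is non-collapsible: conditioning on a prognostic covariate changes the quantity estimated even when the absolute effect is the same. If the covariate set is not fixed in advance, neither is the target of the adjusted analysis.

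**Working it through.** **1. The plan's own figure.** From the Sample size section: p0 = 0.85, p1 = 0.95, m = 12, κ = 0.05, 95% confidence (taken as two-sided 5%), 80% power. The Hayes and Bennett formula for clusters per arm is

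c = 1 + (1.96 + 0.8416)² × [p0(1−p0)/m + p1(1−p1)/m + κ²(p0² + p1²)] / (p0 − p1)²

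The bracket is 0.010625 + 0.003958 + 0.004063 = 0.018646, so c = 1 + 7.849 × 0.018646 / 0.01 = 15.63. That gives 16 clusters, and 15.63 × 12 = 187.6, or 188 cases. This reproduces "we would need 16 clusters and 188 culture-positive TB cases in each arm to detect this difference with 95% confidence and 80% power".

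**2. Information available for adjustment.** Expected non-initiations are 188 × 0.15 + 188 × 0.05 = 28.2 + 9.4 = 37.6, about 38 of 376. With all eight variables entered as single terms plus the arm, that is 37.6 / 9 = 4.2 per coefficient. With three single-term covariates plus the arm it is 37.6 / 4 = 9.4.

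**3. How often chance alone could trigger the rule.** The plan states no threshold, so this is only an illustration. With eight independent candidates, at least one is flagged with probability 1 − 0.95⁸ = 34% at a 5% screen, or 1 − 0.90⁸ = 57% at a 10% screen.

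**4. What the rule does to inference.** The simulation used 3,000 trials per scenario, 16 clusters of 12 per arm, and logistic regression with cluster-robust standard errors. There were eight independent candidate covariates, two of them prognostic with a log odds ratio of 0.4 or 0.7 per SD, and imbalance was flagged at |z| > 1.645. The covariate effects, independence and threshold are assumptions. Ranges run over the two effect sizes.

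| | Unadjusted | Imbalance-selected | Pre-specified |
|---|---|---|---|
| Rejection, 85% vs 85% | 5.8–5.9% | 5.5% | 5.7–6.0% |
| Rejection, 85% vs 95% | 90.9–91.0% | 90.9–91.2% | 91.2–92.9% |
| Mean log OR, 85% vs 95% | 1.246–1.250 | 1.255–1.261 | 1.291–1.372 |
| Mean SE of log OR, 85% vs 95% | 0.395–0.396 | 0.398–0.399 | 0.403–0.417 |

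The unadjusted and imbalance-selected analyses disagreed on significance in 1.1% to 1.7% of trials.

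The Monte Carlo standard error is about √(0.055 × 0.945 / 3000) = 0.4 points for the null rows and √(0.91 × 0.09 / 3000) = 0.5 points for power. The type I error differences are therefore not distinguishable from noise. Pre-specified adjustment gained 0.2 points of power over the unadjusted analysis at the weaker covariate effect (91.2 − 91.0) and 2.0 at the stronger (92.9 − 90.9).

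The simulated power of 91% is not comparable with the plan's 80%. The simulated cluster effect had SD 0.15 on the logit scale, roughly 0.15 × 0.85 × 0.15 = 0.019 on the proportion scale, against κ × p0 = 0.0425 in the plan. Only the comparison between columns is informative.

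**The case against.** The strongest reply is that the primary analysis is already fixed. It is called univariate twice, its estimate, interval and test are specified, and the covariates come afterwards as an addition. A reader might infer from the covariate sentence that the primary odds ratio is itself data-driven; on the natural reading of the text it is not. That reply largely stands. What it leaves open is the reach of *the model* and of the final analyses, and the absence of a statement of precedence.

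Three further inferences are tempting and are not supported.

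- **Lost precision.** Adjusting a logistic model for prognostic covariates raises the standard error of the log odds ratio, as step 4 shows. The possible gain is in power. The documents give no covariate–outcome associations from which to size it.
- **Inflated type I error.** None was visible.
- **A 34% chance of a spurious adjustment.** The plan states no significance screen, requires a characteristic to be important as well as unbalanced, and lists variables that are plainly related (HIV status, CD4 count, ART use).

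It can also be said that thresholds and covariate lists belong in an analysis plan that is not shown. Their absence is indeed no fault. The point is the rule that the article does state: observed imbalance decides.

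Finally, imbalance here may be systematic. Allocation is communicated before each two-week block, and the Discussion acknowledges possible differential recruitment and non-participation. That is a good reason to adjust, but it favours naming prognostic covariates in advance, since they are then adjusted for whether or not a check flags them.

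**Conclusion.** The point holds for the adjusted analysis. Its covariates are chosen by observed between-arm imbalance, and the article does not say clearly which result governs if it differs from the univariate one. It does not show that the primary test is invalid.

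The size is small: disagreement on significance in 1.1% to 1.7% of simulated trials, and about 0 to 2 points of power from a pre-specified set. These figures rest on the assumed covariate effects, independence and imbalance threshold, and on less between-cluster variation than the plan assumes. The main benefit of the change is freedom from a data-driven choice of model, not a narrower interval for the odds ratio or a corrected error rate. It is worth making because it costs almost nothing.

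**What to change.** Amend the Statistical analysis wording before any comparison by arm is made:

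1. Delete the imbalance trigger in both places where it appears. Keep the baseline table as description.
2. Name a short list of prognostic covariates already collected, for example previous TB, a combined HIV/CD4 category and age, and adjust for them whatever the observed balance. About 38 expected non-initiations allow only a few coefficients.
3. State that the univariate GEE model, or alternatively the named adjusted model, governs the conclusion and that the other is supportive.
4. Confine adjustment for any other imbalance to a sensitivity analysis labelled as such.
5. Optionally, report a standardised risk difference with its interval beside the odds ratio. The design is framed as 85% against 95%, and this measure keeps the same target with or without covariates.

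The cost is wording; no new data are needed and the sample size is unchanged. A fixed list also moves the target of the adjusted odds ratio away from the univariate one, but in a way known beforehand. The downside is that an imbalance in an unlisted variable is dealt with only in the sensitivity analysis.
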